AIMS and Bayley Scales are recommended to use together and in different ages because false positives are common and therefore it is beneficial to follow-up children at high risk of motor impairment at more than one time point, or to use a combination of assessment tools [8].

Secondary outcome: We have evaluated parental stress and parental infant bonding at hospital discharge in all preterm infants included in the study and survival in the neonatal period.

PARENTAL BONDING INSTRUMENT (PBI) had been applied by a professional blind to the group to which the child belongs. These questionnaires are to be used for research purposes only. PBI is a self-administered Likert scale (0 to 3) instrument, with 25 questions related to father and mother, in which subjects answer how similar those behaviors were to their parents’ behavior until the age of 16 years. The instrument measures two constructs: the first one is affection, which is more consistent and clearly bipolar (affection, heat, availability, care, sensitiveness versus coldness and rejection); the second construct is control or protection (control, intrusion versus encouragement of autonomy) [20].

Emotional availability scales –EAS: this scale will be used to assess both groups at the end of the study. The EAS consists of six scales; four scales assess adult emotions and behavior related to sensitivity, structuring, non-intrusiveness, and non-hostility. The other two scales are related to child behavior. Child responsiveness to the caregiver assess the child interactions with the adult; and child involvement with the caregiver scale assesses the behaviors regarding to child invitations to caregiver to join her in the play and the interaction talks with the caregiver. The scales scores are obtained by scores measured in each dimension using a Likert-type continuous scale with scores between 1 and 7.

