To implement a program of continuous and global intervention for preterm infants to be delivered by their families	Improve interaction parental infants since neonatal period with massage therapy by mothers Decrease parental stress Improve neurodevelopment at 12 to 18 months corrected age	During the whole study period. It start one month after receive the grant. There are meetings with the team during the study. All teamneed to be trained to teach the tactile-kinesthetic stimulation by mothers and home visits. The patients are allocated to the study up to a total of 100 (50 in each group) and sequentially randomized when the patients complete 48 h after birth. Exclusion criteria: congenital malformations and parents’refusing to participate in the study. At the end professionals with training to carry out the testings for development assessments will provide the results.
Objective 2:		
Advise and improve the skills of care givers in respect to children’s needs	Reduce to the minimum the lost for follow up (home visits, phone contacts, phone calls) Decrease parental stress that will be measured previously Improve parental infant bonding that will be measured in the beginning Home visits to be sure that the interventions are performed	Patients are randomized to two groups. At admission of the study the intervention will promote a moment of care and further interaction through massage therapy performed by mothers. Following consist of guidelines and measures to promote early intervention with parents’ orientation independently of f the standard evaluation and care that will be performed. There will be daily sessions of 10 to 5 min each one in NICU and three times a week (motor stimulation), daily (cognitive stimulation) at home.
Objective 3:		

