Evaluate the impact of the intervention in the neurodevelopment of the children	More strengthened ties to the program start, as measured by PBI resulting in higher scores of attention, care and protection . Number of patients with the Bayley III scale normal for corrected age Number of patients with AIMS scale normal for corrected age. Statistical measures of the differences between the groups (intervention and conventional approaches).	At discharge of neonatal unit (PBI) we will have the first evaluation. After 10 sessions and home visits we will have the follow up evaluations. AIMS and Bayley III Scales at 12 to 18 months corrected age A global neurodevelopment evaluation will be obtained at 12 to 18 months corrected age for all patients.

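### The Parental Bonding Instrument, as the protocol describes it, records the parents' own upbringing, so it cannot serve as the discharge parent-infant bonding outcome or as evidence of the intervention's impact

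*Protocol article*

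**What the plan says.** The secondary-outcome paragraph under Outcomes in the protocol article states: "We have evaluated parental stress and parental infant bonding at hospital discharge in all preterm infants included in the study". The next paragraph gives the format of the PBI: "PBI is a self-administered Likert scale (0 to 3) instrument, with 25 questions related to father and mother". On what the items ask, it presents the PBI as a form "in which subjects answer how similar those behaviors were to their parents’ behavior until the age of 16 years". It gives the instrument two constructs. The first is affection; of the other it says "the second construct is control or protection (control, intrusion versus encouragement of autonomy".

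The participant timeline that accompanies Fig. 1 repeats the assessment of bonding at discharge. Table 2 then uses the PBI in two ways:

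- Under Objective 3, which concerns the impact of the intervention, the listed outcome is "More strengthened ties to the program start, as measured by PBI resulting in higher scores of attention, care and protection".
- In the same row, the timing is "At discharge of neonatal unit (PBI) we will have the first evaluation".

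Objective 2 of Table 2 adds "Improve parental infant bonding that will be measured in the beginning", without naming an instrument.

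A second relationship measure, the EAS, is described under Outcomes and is to be used in both groups at the end of the study.

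**The concern.** The protocol says what the questionnaire asks and what it is meant to show, and the two do not match. The questions look back to the respondent's childhood and to the respondent's own mother and father. The intended conclusion is about the tie between that respondent and a newborn.

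The PBI is the only bonding instrument named for discharge. If the two arms score alike, the trial may report that the in-hospital programme left bonding unchanged. If they differ in the hoped-for direction, it may report stronger ties. Neither statement would follow from the data.

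The protection subscale adds a second difficulty. Table 2 treats a higher score as success, yet the protocol's description of the construct puts control and intrusion at one end. A result could be presented as favourable when the instrument means the opposite.

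**Working it through.** No arithmetic applies. The check sets the protocol's statements side by side.

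1. **Who answers, and about whom.** The PBI is self-administered (Outcomes). The study child is a newborn at discharge, so the respondent must be the mother or father. The behaviour being rated is that of the respondent's parents, up to the respondent's age 16. The study infant does not enter the questions.

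2. **When the measured quantity was fixed.** Randomization is at 48 hours after birth, and massage by the mother starts on day 7 of life (Interventions; timeline with Fig. 1). The recall window closes at the respondent's 16th birthday. For any respondent of 16 or older it had closed before the infant was randomized, so nothing delivered in the trial can alter what is being asked about.

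3. **What a difference between arms could mean.** Three sources remain:
   - chance;
   - imbalance between arms in the parents' backgrounds;
   - a change in how parents report the past.

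   The third is a practical possibility. Intervention mothers give the massage themselves and meet researchers every 48 hours (Intervention group), and parents sign a further consent form that depends on their group (Ethics and dissemination). The professional who applies the form is blind, but that does not blind the person who fills it in.

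4. **What the protocol does with the score.** It serves as the discharge bonding outcome (Outcomes) and as an impact indicator, "as measured by PBI resulting in higher scores of attention, care and protection" (Table 2, Objective 3). Steps 1 to 3 support neither use.

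5. **Direction of the protection score.** Table 2 takes higher as better. Outcomes names the construct control or protection and lists control and intrusion first, against encouragement of autonomy. The affection construct is likewise named after its first-listed, warm pole. By that pattern a high protection score would mean more control. The EAS, in the same section, scores non-intrusiveness. The protocol never says which end of the protection scale scores high, so this step shows an apparent inconsistency and does not prove a reversal.

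6. **Timing, for any alternative use.** The only stated time for the PBI is discharge, described as the first evaluation. That is after randomization and after the unblinded in-hospital intervention.

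**The case against.** The strongest reply is that this is one secondary instrument in a trial whose primary outcome is Bayley III and AIMS at 12 to 18 months, with a sample size based on development scores. The relationship is also covered elsewhere: the EAS is given in both groups, and feeding at 6 months corrected age is recorded as a reflection of maternal bond. A null PBI result would therefore not stand alone. This is right about scale, and it limits the point to a secondary outcome. It does not make the PBI valid for discharge, where no other bonding instrument is named.

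A second reply is that an article leaves detail to the full protocol. The problem here is not an omission: the article states both the content of the questionnaire and the use made of it, and these conflict.

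A third is that recalled answers may move with present mood. They may, but a shift in how a mother remembers her own parents is not a closer bond with her infant.

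Three stronger readings are tempting and are not supported:

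- A reader might infer that the protection score is definitely reversed. The scoring direction is not stated, and the inference rests on how the poles are named and ordered.
- A reader might infer that a test on the PBI has power equal to its 5% significance level. That would require reports not to shift by arm, which step 3 puts in doubt. It would also require independent responses, yet twins and triplets go to the same arm, so one mother's answers could be counted more than once if the analysis is per infant.
- A reader might infer, partly from Table 2's remark that bonding is measured "in the beginning", that the PBI can be kept as a baseline covariate or moderator. Its only stated timing is discharge.

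**Conclusion.** The point holds for the construct. As the protocol describes it, the PBI measures something settled before randomization and unrelated to the study infant, so it can support no conclusion about parent-infant bonding or about the impact of the programme. The protection direction in Table 2 appears inconsistent with the Outcomes section, and the two must be reconciled.

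The consequence is an uninterpretable discharge bonding result and one unsound impact indicator. The Bayley III and AIMS outcomes, the sample size and the randomization are untouched, and no numerical statement about power is made.

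The conclusion rests on two assumptions. The first is that the article describes the questionnaire as it is actually given. The second is that respondents are 16 or older; the article sets no minimum maternal age. For a younger mother the recall window would still be open, but the questions would still concern her own parents and not her infant.

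**What to change.** Before analysis, and with the change and its reason disclosed:

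- Remove the PBI as a bonding outcome in the secondary-outcome text and as an impact outcome in Table 2, Objective 3. Bring the timeline and Table 2, Objective 2 into line.
- Report the PBI only as a description of parental background. Do not use it as a baseline covariate or moderator, because it is completed at discharge after unblinded intervention.
- Delete higher protection as a sign of benefit, and state the scoring direction of both PBI constructs wherever the scores are reported.
- Name the EAS, already planned in both groups at study end, as the parent-child relationship outcome.

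No new form or visit is needed, but the cost is more than wording. The trial is registered and recruiting, and the text indicates that the PBI has already been applied, so a secondary outcome is being reclassified mid-trial and this must be justified openly. No valid bonding measure then remains at discharge, and the report should say so.

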**Fig. 1 Fig1:**
[figure not shown]
Study flow chart. The flow chart of enrolment, allocation, intervention and assessment. *Intervention Group has ten additional appointments for systematic orientation for a continuous global simulation at home and ten home visits

Sample size: the sample size was calculated on the basis of the results of many studies that assessed improvement of motor and mental development or cognitive or language acquisitions. All these studies obtained minimum scores 20% higher after early intervention. For a 5% level of significance and a statistical power of 80%, a sample size of 84 patients will be required to detect a 3-point between-group difference in development scores [20, 24–26]. The allocation of the subjects will be perfomed until the complete calculated sample size based on the number of premature infants who survive until hospital discharge. A number of 20% (number 16) will be added, considering possible loss or death during the follow-up. Total sample size will be 100 preterm infants.

Recruitment: strategies for achieving adequate participant enrolment to reach target sample size will be: to establish a link between the research team and mother and father of each of the subjects included, regardless of the group allocated since randomization. Weekly meetings are performed during NICU stay.

A telephone number is available twenty-four for all questions after discharge and during the follow up. This mobile phone stays each day with a researcher’s member on call to resolve doubts with clarity and security. A prior scheduling of home visits and office appointments is done continuously during the recruitment and assessment according the objectives.

Assignment of interventions: Monitoring the progress of this research is fundamental for assuring that all activities will be achieving stated milestones. The selection of adequate method for generating the randomization sequence is important for result measurements. We have used the research randomizer program available at www.randomizer.org [23].

Simple randomization method for allocation: computer-generated random numbers for each 5 participants determines the allocation group. The trial is monitored during the process to have a balance in the number of subjects on each arm over time, eg, twins, triplets; they will be allocated for the same group. We have not stratification by gender, gestational age, or any other variable. In neonatal period, preterm infants will be sequentially randomized when they completed 48 h after birth. Randomization is performed by researchers that will not be responsible for any intervention, nor outcome measures of parental bond, motor and cognitive outcomes. The same researchers will register all neonatal data, discharge variables and the follow-up data, during the appointments (not blinded). During the NICU stay period, the nursing and the medical staff were informed that participating infants would receive an active intervention by the mothers depending on group allocation (not blinded). The data analysts, outcome assessors and the multidisciplinary team working in the institutional follow up clinic will be blinded.

The allocation of the subjects will be maintained until the complete sample size calculation. Both arms are routinely candidates for outpatient institutional follow-up clinic.

Data collection, management and analysis are being presented according checklist [23].

Data collection: Clinical morbidities and identification data were prospectively collected in duplicate during hospital stay until hospital discharge for the two independent researchers.

Both groups have all data obtained during regular appointments at the outpatient follow up clinic masked for allocation of patient groups. All variables will have double data entry in data record center storage.

Neonatal variables include maternal and perinatal characteristics and short-term outcomes. The maternal characteristics are: age, parity, number of prenatal visits, gestational diabetes, chronic hypertension or preeclampsia, chorioamnionitis or urinary tract infection, household income and educational level. The neonatal variables are: gender, type of delivery, 1 and 5 min Apgar scores, surfactant use (at least one dose), antenatal corticosteroid use, gender, gestational age (evaluated by the last menstrual period and confirmed by an early obstetrical ultrasound and neonatal clinical examination), birth weight and small-for-gestational-age status (defined as a birth weight below the 10th percentile), and the Neonatal Acute Physiology and Perinatal Extension II (SNAPPE II) score. The presence of Respiratory Distress Syndrome, bronchopulmonary dysplasia, apnea of prematurity, early or late onset sepsis as confirmed using positive blood cultures, meningitis, necrotizing enterocolitis, patent ductus arteriosus, perintraventricular hemorrhage and periventricular leukomalacia (as determined by brain ultrasound and confirmed using magnetic resonance imaging during the follow-up period within the first 12 months of corrected age), retinopathy of prematurity and universal neonatal hearing screening evaluation (otoacoustic emissions- OAE) during the neonatal period and BERA until six months of corrected age have been also assessed in both arms.

During the follow up three pediatrician/neonatologist will be evaluating monthly, until 6 months of corrected age (CA), bimonthly from 7 up to 12 months corrected age, and every 3 months thereafter until age 24 months, according to routine hospital practice all very low birth weight infants of the study. According randomization conventional group will have standard care of a traditional follow up clinic taking care of the demands according to their necessity and the intervention group, will receive orientation for a continuous global simulation at home besides the usual appointments to the follow up clinic (as previously presented), monthly in the first semester corrected age and bimonthly in the second semester until 12 months corrected age and every 3 months thereafter until age 24 months corrected age. Multidisciplinary team will participate of these activities all the time. All these data can be found in the protocol.

Growth velocity will be registered in the reference curves, using the two computers with an appropriate statistical program for nutritional assessment (ANTHRO). There are two nutritionists to perform the growth evaluations in the exact moments in each group (blinded to which group the child was previously allocated). In the Intervention Group there will be a Nutritionist that will make home visits with the team to reinforce breastfeeding practices. The research team is using a check list during the home visits to the Intervention Group; home visits should be done at least two more researchers.

Statistical methods: All analyses will be performed in the PASW Statistics® for Windows, Version 18.0 software environment (Chicago, IL: SPSS Inc. Released 2009). Qualitative variables will be expressed as absolute and relative frequencies. Pearson chi-square test will be employed to determine the association between categorical variables, with adjusted residuals in case of statistical significance.

Symmetrically distributed continuous variables will be described as means and standard deviations, while asymmetrical distributed categorical variables being described as medians and interquartile ranges. Fisher’s exact test for comparison of categorical variables and Student’s t or the Mann–Whitney tests for comparisons of symmetrically distributed quantitative variables and asymmetrically distributed variables, respectively will be used. Subgroup and any additional analyses will be performed to adjust for social status, maternal age and some preterm’s neonatal conditions associated with poor neurodevelopment outcome.

Monitoring: There are five researchers to monitor data without competing interest. All researchers are independent from sponsor. Data are continuously monitored during the study. The teaching activities and educational programs for the families will be the focus of our research group throughout the study and if some adverse events occur, will be reported. Previous published study showed that the intervention during NICU stay is safe; the 10 additional appointments and 10 home visits will check the intervention safety [23].

Table 2 summarizes the project framework regarding specific objectives, outcomes and period of activities.

**Table 2 Tab2:** Project Framework: specific objectives, outcomes and period of activities

Specific Objectives	Outcomes	Period acticvities
Objective 1:		
To implement a program of continuous and global intervention for preterm infants to be delivered by their families	Improve interaction parental infants since neonatal period with massage therapy by mothers Decrease parental stress Improve neurodevelopment at 12 to 18 months corrected age	During the whole study period. It start one month after receive the grant. There are meetings with the team during the study. All teamneed to be trained to teach the tactile-kinesthetic stimulation by mothers and home visits. The patients are allocated to the study up to a total of 100 (50 in each group) and sequentially randomized when the patients complete 48 h after birth. Exclusion criteria: congenital malformations and parents’refusing to participate in the study. At the end professionals with training to carry out the testings for development assessments will provide the results.
Objective 2:		
Advise and improve the skills of care givers in respect to children’s needs	Reduce to the minimum the lost for follow up (home visits, phone contacts, phone calls) Decrease parental stress that will be measured previously Improve parental infant bonding that will be measured in the beginning Home visits to be sure that the interventions are performed	Patients are randomized to two groups. At admission of the study the intervention will promote a moment of care and further interaction through massage therapy performed by mothers. Following consist of guidelines and measures to promote early intervention with parents’ orientation independently of f the standard evaluation and care that will be performed. There will be daily sessions of 10 to 5 min each one in NICU and three times a week (motor stimulation), daily (cognitive stimulation) at home.
Objective 3:		
Evaluate the impact of the intervention in the neurodevelopment of the children	More strengthened ties to the program start, as measured by PBI resulting in higher scores of attention, care and protection . Number of patients with the Bayley III scale normal for corrected age Number of patients with AIMS scale normal for corrected age. Statistical measures of the differences between the groups (intervention and conventional approaches).	At discharge of neonatal unit (PBI) we will have the first evaluation. After 10 sessions and home visits we will have the follow up evaluations. AIMS and Bayley III Scales at 12 to 18 months corrected age A global neurodevelopment evaluation will be obtained at 12 to 18 months corrected age for all patients.

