### Outcomes

Primary outcome: a global neurodevelopment evaluation will be obtained at 12 to 18 months corrected age for all patients to compare the effect of early systematic intervention independently of formal enriched environments in motor and cognitive aspects. The infants will be evaluated in relation to their motor, and cognitive neurodevelopment using AIMS and Bayley III scales between 12 and 18 months corrected age [14–16].

AIMS (Alberta motor infant scale): a blinded physiotherapist will evaluate the children of both groups between 12 and 18 months with Alberta Infant Motor (AIMS) scale in all eligible patients. The evaluation will be conducted in the presence of parents or caregivers in a safe surface with room for the child move around during the evaluation. The examiner will interact with the child to encourage response, but physical facilitation of movement should be avoided. During the evaluation, they are punctuated behaviors more or less mature within the motor repertoire of the child in each position (supine, prone, sitting and standing). This repertoire is called “motor” window. All items priced within the window motor and the window motor to the previous items are scored. The evaluation of the end, the child will receive a score based on the sum of the items scored on each posture, called raw score. This score will be observed in a standardized chart to find the baby development percentile according to the chronological age or corrected. Percentiles instrument standards are: 5%, 10%, 25%, 50%, 75%. According to this percentile baby’s development can be classified into three categories: normal or typical (percentile> 25%), suspicious (percentile> 5% and ≤ 25%), abnormal or atypical (percentil≤5%) [14].

BSDI-III: *Bayley scales of infant and toddler development third edition*: The Bayley Scales of Infant and Toddler Development, Third Edition, will be used for assessment of neurodevelopment at 12 and 18 months’ corrected age. The scales will be administered at the hospital clinic, on the same day of each follow-up visit, by a psychologist who was blinded to group allocation. Cognitive, motor, and language development will be considered normal if higher than 89; below average if 80 to 89; borderline if 70 to 79; and extremely low if less or equal 69. Examine all the facets of a young child’s development according manual [15].

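### The printed sample-size figures do not agree: 84 infants and 3 points imply an SD of about 4.9, 3 points is far from a 20% gain on the Bayley scale, and 100 less 20% leaves 80, not 84

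*Protocol article*

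**What the plan says.** The sample-size paragraph (Protocol article, under Outcomes, after the Fig. 1 legend) gives its basis as earlier studies of early intervention: "All these studies obtained minimum scores 20% higher after early intervention". It then sets 5% significance and 80% power and concludes that "a sample size of 84 patients will be required to detect a 3-point between-group difference in development scores". The allowance for attrition follows: "A number of 20% (number 16) will be added, considering possible loss or death during the follow-up". The total is 100, which Table 2 splits as 50 per group.

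The paragraph does not say which development score is meant, what SD or control mean was used, or whether the test is one- or two-sided. The Outcomes section makes AIMS and Bayley III together the primary assessment. It gives no mean or SD for either, but it does show the range in which Bayley scores are read: "Cognitive, motor, and language development will be considered normal if higher than 89; below average if 80 to 89", with lower bands at 70 to 79 and at 69 or less.

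**The concern.** This paragraph is the only justification for the size of the trial. It offers two effect sizes, a relative one (20%) and an absolute one (3 points), and on the Bayley scale they differ several-fold. Only the absolute one is attached to the number 84, and that number fixes the SD that must have been assumed. A reader who wants to know what the trial can detect has to back-solve that SD and then judge whether it suits a score the paragraph does not name. If the score is a Bayley composite and its SD is well above the implied value, the power printed for 3 points is far too high. The enrolment figure also does not deliver the evaluable number stated as required once the planned loss has occurred.

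**Working it through.** **Inputs.** From the sample-size paragraph: alpha 0.05, power 0.80, difference 3 points, 84 required, 20% loss, 100 enrolled. From Table 2: 50 per group, so allocation is 1:1 and 84 is the total (42 per arm). From the Outcomes section: Bayley bands at 69/70, 79/80 and 89/90. Not given: SD, control mean, sidedness. A two-sided test is assumed, with one-sided shown as a variant.

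**1. Reproducing 84.** With no SD it cannot be computed forward, so solve for the SD.
- Normal approximation: detectable d = (1.960 + 0.842) × √(2/42) = 2.802 × 0.2182 = 0.611, so SD = 3 / 0.611 = 4.91.
- Noncentral t: d = 0.619, so SD = 3 / 0.619 = 4.85.
- Forward check with SD 4.9: n per arm = 2 × 2.802² × (4.9/3)² = 15.70 × 2.668 = 41.9, rounded up to 42, or 84 in total. The printed figure is recovered.
- One-sided: d = (1.645 + 0.842) × 0.2182 = 0.543, so SD = 5.5.
- Reading 84 as per arm would allow an SD of 6.9, but a total of 100 rules that reading out.

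**2. If the SD is larger (assumed values; t-test, 42 per arm, two-sided).**

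| Assumed SD | Power for 3 points | Difference with 80% power (0.619 × SD) |
|---|---|---|
| 10 | 27% | 6.2 |
| 12 | 20% | 7.4 |
| 15 | 15% | 9.3 |

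By the normal approximation, 80% power for 3 points would take 350 infants in total at SD 10 and 786 at SD 15.

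**3. 20% against 3 points.** At Bayley control means of 70, 80 and 90, 20% is 14, 16 and 18 points. Three points is 3/70 = 4.3% to 3/90 = 3.3% of such a mean. On any scale, 3 points equals 20% only where the mean is 3/0.20 = 15, and the document mentions no such score. Nor does the relative effect lead to 84 with a similar SD: 16 and 18 points with 42 per arm imply SDs of 16/0.611 = 26 and 18/0.611 = 29.

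**4. Loss allowance.** 84 × 1.20 = 100.8, so 100 comes from adding about 20% to the required number. But 20% of those enrolled are then lost: 100 × 0.80 = 80 evaluable, which is 4 short. Keeping 84 after 20% loss needs 84/0.80 = 105. Equivalently, 100 enrolled covers (100 − 84)/100 = 16% loss. At the implied SD, 40 per arm gives about 78% power rather than 80%. The standardised difference with 80% power moves from 0.619 to 0.634.

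**The case against.** The strongest reply is that nothing printed shows an SD of 4.9 to be wrong. The score is left unnamed; AIMS is also a primary instrument and yields a raw score summed over items; and the document gives no SD for either scale. This stands. A reader might infer that the SD cannot be 4.9 and that the trial therefore lacks its stated power on its primary scale. The documents do not support that: they name two instruments, and a Bayley SD of 10 to 15 is an assumption brought in here. The power figures in step 2 are conditional on it.

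It can also be said that an article condenses a full protocol, so a missing SD or scale name is only an omission. By itself that is fair. The point here is that the printed figures disagree: the relative effect against the absolute one on the Bayley scale, and the evaluable number after loss against the number required.

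Third, the text never says that 3 points is the 20% gain, and the 20% may describe change after intervention in earlier studies. That is possible, but the paragraph presents it as the basis of the calculation and gives no link to 3 points.

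Fourth, adding 20% to 84 is a common convention and costs about 2 points of power. This is why the loss allowance is the lesser part.

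Finally, any replacement figure has limits of its own. The allocation paragraph sends twins and triplets to the same group, so a calculation that treats infants as independent is slightly optimistic. Table 2 also lists counts of infants in the normal range, which a detectable mean difference does not cover.

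**Conclusion.** The point holds as an inconsistency among printed figures. With 42 per arm, 80% power for 3 points requires an SD of about 4.9 (5.5 one-sided), and the paragraph gives no score or SD against which to check this. On the Bayley scale at scores of 70 to 90, the cited 20% is 14 to 18 points, roughly five to six times the 3-point target, and the two are not reconciled. Under an assumed Bayley SD of 10 to 15, power for 3 points would be about 27% to 15%, and the difference detectable with 80% power about 6.2 to 9.3 points. The loss allowance is a minor error: 80 evaluable instead of 84, about 78% power instead of 80% even at the implied SD.

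A reader might go further and infer that a null result would be taken to exclude a 3-point benefit. The documents do not support that step, since a confidence interval would show what is excluded.

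**What to change.** Keep 100 infants and correct the paragraph:
- Name the score to which the calculation refers, and state its assumed SD with a source.
- Restate the detectable difference with 80% power at two-sided 5% as about 0.62 SD for 84 evaluable infants, or about 0.63 SD for 80 evaluable after 20% loss. Add that this treats infants as independent and is slightly optimistic because twins and triplets are allocated together.
- Reconcile the 3-point target with the 20% rationale on the named score, or delete both.
- State the loss allowance as 16%, or keep 20% and give the evaluable number as 80.

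The cost is protocol wording and a less favourable stated detectable difference. No extra infants are needed and the design does not change.
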